### Data management and security

There are 12 Excel files that are generated during each visit in which data are collected. Those files are later combined into a single zip file. Consequently, there are three zip files created for each participant - each one containing the 12 Excel files from one of the visits. Once a zip file is created following a visit, it is uploaded into the STaRS system.

At the PCCR, the zip file is downloaded from STaRS and stored on a secure file server on the PCCR network. All PCCR servers reside behind a state-of-the-art firewall with permissions determined by Active Directory. Through the use of a custom-developed macro in Excel, the individual data points are taken from each Excel data file and copied into a single large Excel file that acts as a database containing all of the data from all of the Excel data files. There is a separate sheet in the database file for the data of each type of test that generates an Excel data file: simple hand reaction time, simple foot reaction time, choice reaction time, and Fitts’ law data. In addition, there is a fifth sheet that also contains the choice reaction time data, except that in that sheet there are blanks instead of data for those choices that were incorrect. For example, in the case when the test presented a prompt that called for a response with the left hand, but the participant used the left foot instead of the left hand. Generating a sheet of the choice reaction time data in this manner provides the opportunity for that data to be analyzed excluding times from incorrect choices, as described by Whelan [26].

There is one line created in the database file for each repetition of each type test with all of the data from that test. That line also contains the participant ID, visit number (1, 2, or 3), the type of test, which repetition of the test for that visit (1, 2, or 3), the date the test was given, and the name of the data file from which this particular set of data originated. In addition, the sheets for the choice reaction time test also include the number of incorrect choices that were made on that instance of the test.

A custom macro for Excel was developed to permit t-wall data for a given visit that had been hand-written on the hard copy checklist to be key-entered into an electronic form that has a field for each bit of data. The data thus entered consists of the participant ID, visit number, repetition number of the t-wall test on that visit, and the three times that were taken to complete the three repetitions of the t-wall test in that visit. The macro places the values on the electronic form into the correct places in an Excel file that serves as a database for all the t-wall data. In that database file there is one line for each participant. That line contains all of the t-wall data for that participant along with the participant ID and the date of each visit in which data was collected. Quarterly onsite audits are made by the PCCR project manager to ensure that the times of all repetitions of the t-wall tests, as manually written on the data collection forms, have been accurately entered into the computer.

Excel database files are backed up monthly and placed on two other hard drives. The data core manager writes programs in the SAS System for Windows (Release 9.4; SAS Institute Inc., Cary, NC, USA) using SAS ACCESS to create the analyzable datasets and creates the data dictionary. Only the data core manager and biostatisticians will have access to the datasets.

### Statistical methods

An intention-to-treat approach, in which participants will be analyzed according to their original treatment allocation, will be used. All observed data will be used in the analyses. Data analyses will be performed using SAS. The level of significance will be set at 0.05. Descriptive statistics of participant baseline characteristics, the reaction and response times and the PROMIS-29 scales at visit 1 will be presented for each treatment group.

The primary analyses compare the mean changes in reaction and response times from sequence A, performed before CMT/break at visit 2, to sequence A performed before CMT/break at the final visit between the treatment and wait-list control groups, using an analysis of covariance controlling for age, for each of the five biomechanical tests. Residual plots will be used to assess the validity of the model assumptions. If group variances are heterogeneous, we will use a mixed-effects regression model. If the data is non-normal, we will explore data transformations. Mean differences between groups, adjusted for age, will be reported with 95 % confidence intervals.

The secondary analyses will compare the immediate changes in sequence A before CMT/break to sequence A after CMT/break at both visit 2 and the final visit using the same methods described above.

Although we do not expect changes in the PROMIS-29 Health Survey scales or medication use in this short time frame, we will explore it by analyzing changes from visit 1 to the final visit.

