**Methods:**

This study is a randomized controlled trial of 120 asymptomatic volunteer SOF personnel. All participants are examined by a study doctor of chiropractic (DC) for eligibility prior to randomization. The participants are randomly allocated to either a treatment group receiving four treatments of chiropractic manipulative therapy (CMT) over 2 weeks or to a wait-list control group. The wait-list group does not receive any treatment but has assessments at the same time interval as the treatment group. The outcome measures are simple reaction times for dominant hand and dominant foot, choice reaction time with prompts calling for either hand or either foot, response time using Fitts’ law tasks for small movements involving eye-hand coordination, and brief whole body movements using the t-wall, a commercially available product. At the first visit, all five tests are completed so that participants can familiarize themselves with the equipment and protocol. Assessments at the second and the final visits are used for data analysis.

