There have been two changes in the eligibility criteria since this study began. Originally, the upper age limit was set at 45 years. However, as recruitment progressed it became apparent that SOF included members over the original age limit with an interest in the study. Consequently, it was decided to allow those who were still active in SOF to participate with no upper age limit. The second change allowed women to participate in the study. Initial study recruitment was limited to personnel who were not only in SOF, but were also special forces-qualified – a subset of SOF personnel who could not be female. In order to meet the required rate of recruitment, it was necessary to broaden the scope of eligibility to include members of the Special Operations Aviation Regiment who are on flight status, which includes female pilots. Both changes were approved by all IRBs involved in this study. The changes were made after 41 participants had been enrolled in the study.

### Between visit 1 and visit 2

The data from visit 1 is entered into STaRS. If all eligibility criteria are met, the participant is randomly allocated to either the treatment group or the wait-list control group. Group assignment is done using concealed allocation in a 1:1 ratio by a predetermined, computer-generated, restricted randomization scheme with random block sizes of 2, 4 or 6. The site PM has no knowledge of any details of the randomization process but accesses the group allocation module within STaRS to retrieve the participant ID and assigned group. The group assignment and date, time, and study participant ID are stored in the Structured Query Language (SQL) database. If the STaRS database is unable to be accessed when a participant needs to be allocated to a group, there is a backup allocation protocol consisting of predetermined sequentially numbered, opaque envelopes. Once allocation has been made to either the treatment group or the wait-list control group, the participant is called or sent a text message specifying their group assignment. Personnel at the PCCR who process the raw data are blinded to which group individual participants have been allocated to and will remain blinded until after completion of the study.

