## Discussion

SOF personnel as a group are likely to be in need of reaction and response times that are as quick as possible during the course of their assigned duties. One goal of CMT is to maximize the integration and function of the neuromusculoskeletal systems. Therefore, this intervention is well-suited for attempting to optimize the capacity of the numerous components involved in the production of a minimal reaction and response time. This study is designed to show if CMT will result in quicker reaction and response times for those SOF personnel who receive it. The results of the study will be published following completion of data collection and analysis.

Two different random but set sequences of prompts for each of the five biomechanical tests were used to prevent participants from memorizing the sequence and anticipating prompts. However, different sequences can have different levels of difficulty. Consequently, whenever the results of two replications of the same test are to be compared with each other we wanted to have the same sequence of prompts used for those replications of that test. The only replications of each test that are to be used in the data analysis of this study are the ones taken immediately before and after the participant receives a CMT/break. Therefore, for visit 2 and the final visit, the order of prompt sequences and the CMT/break that is used is B, A, CMT/break, A. Having a replication of the test completed using sequence B just before the one with data that will be analyzed that uses sequence A has a double value. Not only does it prevent memorization of the prompt sequence, but it also provides an opportunity for the participant to get in the mode of doing that particular test after doing other, different tests before doing it for analysis.

Once the resulting manuscripts have been published, datasets will be provided for public access. Potential investigators can contact one of the co-PIs to present their hypothesis, study design, instruments and/or data on which to focus, and resources required. Depending upon the needs and desires of the requesting party, the data that is shared may include analytic tables or deidentified or limited datasets that are transmitted to the requesting parties for additional analyses. In addition, the trial is registered on ClinicalTrials.gov, making all key information about the trial freely available.

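### The primary change-score ANCOVA adjusts only for age; adding the visit 2 time of the same test would gain precision at almost no cost

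*Protocol article*

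**What the plan says.** In the protocol article, the Statistical methods section defines the primary outcome as a change: "The primary analyses compare the mean changes in reaction and response times from sequence A, performed before CMT/break at visit 2, to sequence A" at the final visit, both before CMT or break. The model is fitted "using an analysis of covariance controlling for age, for each of the five biomechanical tests". The reported estimate repeats the covariate set: "Mean differences between groups, adjusted for age, will be reported with 95 % confidence intervals". The secondary comparisons, of immediate change within visit 2 and within the final visit, are made "using the same methods described above", so they inherit it.

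The same section offers a mixed-effects model if group variances differ and transformations if the data are not normal. Neither fallback is said to bring in the baseline time.

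The visit 2 time is recorded before the first CMT (Visit 2 section) and is one half of the primary change score. The abstract confirms that "Assessments at the second and the final visits are used for data analysis".

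**The concern.** An analysis of change without the baseline value as a covariate fixes the baseline slope at 1. When the correlation between visits is below 1, that slope is too steep: a group that happens to start slower tends to show more improvement than it would from treatment alone. Part of any chance difference between groups at visit 2 then stays in the estimated effect, and the estimate varies more than it needs to.

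The stake is the width of the five primary confidence intervals, and how far each realised estimate depends on the luck of the visit 2 comparison. The covariate set is stated twice, so this is a choice the protocol makes and not a detail it leaves open.

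**Working it through.** **Inputs from the protocol article.** 50 per group analysed, at least 85% power, a target of 10% of the visit 1 mean, the pilot SD of change, and 120 randomised to allow for 15% loss (Sample size). For alpha: "The level of significance will be set at 0.05" (Statistical methods); sidedness is not stated, and two-sided is assumed. The pilot SDs, the visit 1 means and the correlation r are not given.

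**1. The protocol's own power figure.** It cannot be reproduced without the SDs and means. It can be turned into the standardised effect it implies:

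d = (1.960 + 1.036) × √(2/50) = 2.996 × 0.2 = 0.599 SDs of change (0.605 with the noncentral t).

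The SD of change could then be at most 10%/0.599 = 16.7% of the visit 1 mean. For dropout, 100/0.85 = 117.6, rounded up to 118, so 120 is enough.

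**2. Variance with and without the baseline.** Let the SD at each visit be σ, and let r be the correlation between visits given age. Per participant:

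- change score: 2σ²(1 − r)
- adjusted for baseline: σ²(1 − r²)
- ratio: v = (1 − r²) / [2(1 − r)] = (1 + r)/2

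**3. Power after adjustment**, starting from exactly 85%: Φ(2.996/√v − 1.960).

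**4. Baseline imbalance left in the change estimate.** With equal variances it is −(1 − r) times the visit 2 difference. One standard error of that difference is σ√(2/50) = 0.20σ. The detectable effect is 0.599σ√(2(1 − r)).

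| r (assumed) | v | Fall in SE, 1 − √v | Equivalent extra participants, 1/v − 1 | Power | Shift from a 1 SE imbalance | Shift as % of detectable effect |
|---|---|---|---|---|---|---|
| 0.5 | 0.75 | 13.4% | 33% | 93.3% | 0.10σ | 16.7% |
| 0.7 | 0.85 | 7.8% | 18% | 90.1–90.2% | 0.06σ | 12.9% |
| 0.8 | 0.90 | 5.1% | 11% | 88.5% | 0.04σ | 10.6% |
| 0.9 | 0.95 | 2.5% | 5% | 86.7% | 0.02σ | 7.5% |

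The normal approximation and the noncentral t agree to within about 0.1 percentage point of power.

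**5. Simulation check.** With 20,000 trials of 50 per group at each of r = 0.5, 0.7 and 0.9:

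- The variance ratios were 0.76, 0.86 and 0.96, slightly above (1 + r)/2 because the slope has to be estimated.
- The slope of the change estimate on the visit 2 imbalance was −0.50, −0.30 and −0.10; after adjustment it was about 0.
- With no true effect, both estimators averaged about 0.

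**The case against.** The strongest reply is that nothing is broken. Four stronger readings are tempting, and the document supports none of them.

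- **Bias or invalid tests.** A reader might infer that regression to the mean biases the comparison. It acts in both groups and cancels on average under 1:1 randomisation. Type I error is preserved, and the change-score standard error already includes the variation from chance imbalance. The residual shift is conditional on the imbalance that occurs.
- **Too little power.** The Sample size section uses the SD of change, which is the variance that belongs to the planned analysis. The stated power is also a minimum over five tests, so the gains above apply only to a test exactly at 85%.
- **A serious imbalance is likely.** That depends on the threshold. For five independent tests, at least one imbalance beyond 1 SE has probability 1 − 0.683⁵ = 85%, but beyond 1.96 SE only 1 − 0.95⁵ = 23%. Positive correlation between the tests lowers both.
- **The visit 2 sequence B time is wasted data.** The Discussion restricts which repetitions count: "The only replications of each test that are to be used in the data analysis of this study are the ones taken immediately before" CMT or break, or directly following it. It explains that sequence B serves as a warm-up and guards against memorising, and that sequences may differ in difficulty. Leaving it out is a reasoned choice.

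Two further objections stand as limits. First, r could be high. Each outcome is a mean or total over many prompts, pairs or buttons, follows a practice visit, and is repeated about 10 days later. Near r = 0.9 the gain is slight.

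Second, the visit 2 time is taken before treatment but after disclosure, since between visits 1 and 2 "the participant is called or sent a text message specifying their group assignment". If disclosure moved visit 2 times by δ and the effect then vanished, the change score would carry −δ and the adjusted estimate about −rδ. If it persisted unchanged, the change score would cancel it and the adjusted estimate would keep (1 − r)δ. Neither analysis is favoured in general.

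**Conclusion.** The point holds as a recommended improvement, not as an error that must be corrected. The primary model omits a strong, already collected covariate. Including it would reduce the variance of each estimate by 25%, 15%, 10% or 5% at r = 0.5, 0.7, 0.8 or 0.9, and would remove the dependence on chance differences at visit 2.

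These figures assume equal variances at the two visits, a linear relation, 50 analysed per group and two-sided alpha of 0.05; r is assumed throughout. The algebra is certain, but the practical importance is not, because it depends on a correlation the document does not report. The figures apply to the primary analysis. The visit 2 immediate-change analysis follows the same formula with its own within-visit correlation. They do not carry over to the final-visit immediate change.

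**What to change.** - **Primary models.** For each test, add the visit 2 sequence A time before CMT or break as a covariate beside age. The outcome may stay as change or become the final-visit time; with the baseline in the model, the group difference is identical. Report the difference adjusted for age and baseline with its 95% CI.
- **Immediate change at visit 2.** Add the same visit 2 pre-CMT/break time.
- **Immediate change at the final visit.** Do not adjust for that visit's pre-CMT/break time. In the treatment group it follows three CMTs, so it may itself be affected by treatment. If a baseline covariate is wanted, use the visit 2 pre-CMT/break time.
- **Wording.** State that the visit 2 baseline precedes treatment but follows notification of group. No sequence B covariate is needed.

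The cost is one model term and one degree of freedom per model, with no new data. The Trial status section says data collection ended on 7 June 2016, so the change needs a dated, documented amendment before analysts learn group assignments. If they already know them, keep the planned model as primary and report the baseline-adjusted model as a labelled sensitivity analysis.

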### Sample size

A power analysis used the standard deviations of mean changes in response/reaction time over a 1-week period for each of the five biomechanical variables obtained in the pilot study. We estimated effect size as a 10 % change of the mean response/reaction time measured at visit 1 for each variable, assuming the control group would have no change. A total sample size of 100 participants, with 50 per group, gives at least 85 % power to detect a 10 % difference in mean change between groups at a 0.05 level of significance. We increased the sample size to 120, with 60 per group, to account for the possibility of up to 15 % loss-to-follow-up.

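### Statistical methods leaves the scale of five co-equal primary analyses to be explored after residual plots; one pre-stated log-time model with the visit-2 time as covariate would close the choice and gain some power

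*Protocol article*

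**What the plan says.** In the Protocol article, Statistical methods defines the primary variable as a signed change: "The primary analyses compare the mean changes in reaction and response times from sequence A, performed before CMT/break at visit 2", to the same sequence at the final visit, compared between groups "using an analysis of covariance controlling for age, for each of the five biomechanical tests". Outcome measures states that none of the five tests was singled out as primary, so all five carry equal weight.

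The diagnostic is "Residual plots will be used to assess the validity of the model assumptions". Two conditional steps follow: "If group variances are heterogeneous, we will use a mixed-effects regression model" and "If the data is non-normal, we will explore data transformations". The promised estimate is "Mean differences between groups, adjusted for age, will be reported with 95 % confidence intervals".

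Sample size sets the effect as a 10% "change of the mean response/reaction time measured at visit 1 for each variable", with no change assumed in controls. It states at least 85% power with 50 per group at the 0.05 level, raised to 60 per group for up to 15% loss to follow-up.

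**The concern.** The non-normality rule is open in three respects.

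- **What is transformed.** The modelled variable is a change, which takes both signs. A log or square root cannot be applied to it directly, but can be applied to the two times before differencing. The text does not say which is meant.
- **How the scale is chosen.** No candidate transformation, trigger or selection rule is named. The residuals come from a model that already contains group, so the choice follows a look at the fitted comparison. It could also differ among the five tests.
- **What is then reported.** A mean difference on a transformed scale has no time unit, and no back-transformation is described.

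Separately, the model adjusts for age but not for the visit-2 time, which the trial collects on everyone assessed and which is likely to be the strongest predictor of the final time.

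At stake are a discretionary step in five co-equal tests and some power that could be had at no cost in participants.

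**Working it through.** **1. The plan's own figure.** Inputs from Sample size: 50 per group, difference 10% of the mean, alpha 0.05 (taken as two-sided), power 85%. Solving for the SD of change:

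SD/difference = √(50/2) / (1.960 + 1.036) = 5 / 2.996 = 1.67

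The stated power therefore needs an SD of change of at most 16.7% of the mean (16.5% using the t distribution, 18.6% if one-sided). The pilot SDs are not printed, so the 85% can be neither confirmed nor refuted. The allowance for loss reproduces: 100 / 0.85 = 118, within the planned 120.

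**2. Which quantity can be logged.** The share of negative changes is Φ(−mean/SD).

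- No mean change: Φ(0) = 50%.
- Mean −10%, SD 16.7%: Φ(0.60) = 73%.
- Mean −10%, SD 5%: Φ(2.0) = 98%.

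A log of the change is undefined for half the participants or more. A log of each time is always defined, and the difference of the two logs is a proportional change.

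**3. Power on the log scale.** A 10% reduction is ln(0.9) = −0.105. With 50 per group, √(2/50) = 0.2. At an assumed SD of log change of 0.167:

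0.1054 / (0.167 × 0.2) = 3.16; power = Φ(3.16 − 1.96) = 88.4%

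The same formula gives 94.0% at SD 0.15 and 75.0% at SD 0.20. The log analysis covers about the same SD range as the plan, so the sample size does not change.

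**4. Type I error.** Simulations with 50 per group and lognormal times. All SDs are assumptions, and a Shapiro test at 5% stands in for reading residual plots in the second and third rows.

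| Approach | Rejection under no effect, per test |
|---|---|
| Raw change | 4.6-5.0% |
| Non-normal residuals lead to log times | 4.6-5.2% |
| Non-normal residuals lead to the smallest p of four scales | 4.8-7.1% |
| Most favourable of raw, log and rank, always picked | 6.2-8.1% |

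**5. Power without lapses.** Assumed within-person log SD 0.118 (so the SD of log change is √2 × 0.118 = 0.167) and a true 10% reduction. Let ρ be the correlation between the two log times, that is, between-person variance divided by the sum of between- and within-person variance. Adjusting for log visit-2 time multiplies the variance of the log change by (1 + ρ)/2. For between-person SD 0.15:

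- ρ = 0.0225 / (0.0225 + 0.0139) = 0.618
- SD = 0.167 × √0.809 = 0.150
- power = Φ(0.1054 / (0.150 × 0.2) − 1.96), about 94%

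| Between-person log SD | Raw change (simulated) | Plan's rule (simulated) | Log change (simulated) | ρ | Log time with visit-2 covariate (formula) |
|---|---|---|---|---|---|
| 0.15 | 85.1% | 85.5% | 87.8% | 0.618 | 94% |
| 0.30 | 81.5% | 84.3% | 87.5% | 0.866 | 90% |
| 0.40 | 79.7% | 85.9% | 88.3% | 0.920 | 90% |

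The gains over the plan's rule are about 8, 6 and 4 points. The normal formula runs slightly high: 88.4% against 87.5-88.3% simulated for log change. The covariate supplies most of the gain in the first row and less as ρ rises. Direct simulation of the full model over a range of assumed settings gives 84-94% for the plan's rule and 90-98% for the proposed model, at nominal type I error. The gain across settings is about 2-9 points.

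**6. Power with lapses.** If 10% of whole repetitions are slowed by an average of 0.3 log units, raw change gives 41-43%, the plan's rule 58-64% and the proposed model 66-74%. Power of 42% at a 10% difference implies an SD of change of 10 / (0.2 × (1.96 − 0.20)) = 28% of the mean, about 1.7 times the 16.7% that Sample size requires.

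**The case against.** The strongest reply is that this is a condensed article. The named transformation and its trigger are details usually left to an analysis plan that is not shown. The article already fixes the default model, the diagnostic and the form of the estimate. That is largely right, and it keeps the point small. What stands is that the article does not simply stay silent: it says that the scale will be found by exploration.

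Three stronger readings are tempting, and the documents support none of them.

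- **That the rule cannot be applied to a change score.** The text refers to the data, not to the changes. Logging the times first is a permitted reading and has no sign problem.
- **That type I error is inflated.** The written trigger is non-normality, not a p-value. Followed as written, the rule stays at about 5%. The higher rates describe someone choosing the most favourable result.
- **That power falls to about 42%.** This needs a lapse rate that no section gives and that is in tension with the stated 85%. Each outcome also aggregates 10 or 40 prompts, 32 target pairs or 100 buttons, which dampens single slow responses. The pilot SDs would already include any lapses in the pilot.

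Two further objections hold in part. The planned effect is a fixed fraction of the visit-1 mean, tested as an arithmetic difference, whereas a log model estimates a ratio of geometric means, which is close but not the same. And the remedy adds the visit-2 covariate, a separate improvement; the gain should not be credited to the log scale alone.

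**Conclusion.** The concern holds as an ambiguity and an avoidable data-dependent choice in five co-equal primary analyses. It is not an error in the test: raw change keeps its level, and so does the rule as written. The demonstrated benefit of a fixed model is modest, about 2-9 points of power over the plan's rule without lapses, much of it from adjusting for the visit-2 time. Larger gains depend on an assumed lapse rate without support in the documents. Every power and error figure beyond the plan's own rests on assumed SDs, lognormal times and 50 per group, because the pilot values are not printed. The priority is low, but the change is cheap.

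**What to change.** Trial status reports that data collection is complete, so the change belongs before any unblinded analysis. For all five tests, state:

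- **Model:** log of the final-visit sequence A time before CMT/break, on group, log of the visit-2 sequence A time before CMT/break, and age.
- **Estimate:** the group effect back-transformed to a percent difference with its 95% confidence interval.
- **Sensitivity:** one named analysis, for example a bootstrap interval for the same contrast, and no further search for transformations.
- **Description:** raw-scale differences in time units, reported descriptively.

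The cost is a few sentences, with no new data and no change in sample size. The downside is that the main estimate becomes a ratio of geometric means, so the promised mean differences must be reworded. The log scale does not guarantee well-behaved residuals, and the switch to a mixed model when variances differ remains data-driven unless it is settled separately.
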